### Primary variable

The choice of the primary variable for efficacy is based upon reported findings in the literature.e.g.6,14,40,41 Need for allogeneic blood transfusion is considered to best reflect the blood loss and transfusion frequency in a patient population while other potential primary variables such as length of hospital stay and post-operative haemoglobin values are multi-factorial dependent on for example preferences of the clinic and gender of the patient etc.

The comparison between the treatment alternatives may be biased as it is almost impossible to blind the study. To mitigate the risk of bias the decision of bank blood transfusion will be taken based on transfusion triggers by an assessor unaware of the treatment group whenever possible and the reason/s for the transfusion will be registered. For cases when the decision of bank blood transfusion are taken by a responsible investigator aware of the treatment allocation, e.g. in an emergency situation during surgery, the registered reasons for transfusion will be reviewed by an independent assessor/committee who are unaware of the treatment allocation. Inconsistency in transfusion decision between the independent assessor/committee and the responsible investigator will be reflected in the per protocol analysis where patients with suspected biased transfusion decisions will be excluded. Also post-operative haemoglobin values will be monitored during the study period. In this way systematically inadequate and/or absent allogeneic blood transfusion decisions will be disclosed and addressed during monitoring visits and concerned patients can be excluded from the Per Protocol analysis.

Bleeding volume or complexity of surgery, i.e. surgery time, are considered to possibly influence outcome of the primary variable why stratification for either primary or secondary/revision hip surgery will be made at each recruiting clinic to ensure equal distribution in the two groups. Subgroup analyses of type (primary and secondary) and complexity (easy < 1 hour, medium 1-2 hours and complex > 2 hours) of surgery are planned to further investigate the correlation between the primary outcome and these factors. Age is also a factor that may have an impact on the outcome of the primary variable. It is however considered that randomization as such will ensure approximately equal age distribution in the two treatment groups. Differences in age

between the treatment groups will be evaluated and tested using Wilcoxon rank sum test in the analysis.

### **Comparator**

The control group in the study consists of patients receiving allogeneic blood transfusion based on transfusion triggers and clinical judgement. This is considered as the golden standard since the majority of blood transfusions given in relation to major orthopaedic surgery are allogeneic. Drainages will be placed and used for 24 hours for both treatment groups to standardise post-operative routines and minimise differences between the two treatment groups.

### **3.2.1 Risk/benefit assessment**

The risks for the subjects of using a filtered system for intra- and post-operative blood salvage are mainly related to uncontrolled blood quality. For the Sangvia® system these risks have been addressed by means of extended pre-clinical and clinical studies and extensive clinical experience of autologous blood transfusion in general. The results from studies and experiences indicate that the Sangvia® system is safe to use in man. Any unforeseeable risks of receiving autologous transfusion will be mitigated by monitoring the subjects during the transfusion period. Any signs of a serious clinical event will abort the transfusion. In addition to monitoring the transfusion period the subjects will be closely followed during their hospital stay and checked at 2 months after discharge. All adverse events and complications will be registered.

Allogeneic blood transfusion following major orthopedic surgery has been used for many years because of extensive blood loss leading to postoperative anemia and circulatory complications. The advantages are obvious, e.g. higher oxygen carrying capacity, reduced risk for cardiac, vascular and pulmonary complications etc. However, allogeneic transfusion is also associated with a number of potential risks, errors of matching, immediate and late immune reactions, immune suppression, increased rate of infection, absence of clotting factors and transmission of infectious diseases.

The possible benefits of the study are that the concept of reinfusion of intra- and post-operatively collected and filtered whole blood, in comparison to a group where allogeneic blood transfusion is the only transfusion option, will result in a reduced need for allogeneic blood transfusion and thus leading to lower costs and allogeneic blood related risks.

### **3.2.2 Ethical considerations**

The study will be subjected to ethical review before any subjects are included.

The most important ethical consideration in the design of the current study is the comparative groups, i.e. that subject will be randomized to receive either autologous blood reinfusion or allogeneic blood transfusion when needed based on transfusion triggers. A randomized study of this kind may be considered as unethical but in order to get clinical evidence of treatment efficacy, a prospective, randomized study design is a prerequisite. Also, allogeneic blood transfusion is still considered as the golden standard and the long experience of using autologous blood indicate that this is a safe alternative.

Once a subject is enrolled, he or she has every right to withdraw the consent at any time during the course of the study without being subjected to any disadvantages. The decision to withdraw the consent will not be argued, even though a reason for the withdrawal may be asked for.

### 3.3 Selection of study population

#### 3.3.1 Study selection record

Investigator(s) must keep a record of subjects who were considered for enrolment but were never enrolled e.g., subject screening log. This information is necessary to establish that the subject population was selected without bias.

#### 3.3.2 Inclusion criteria

For inclusion in the study subjects must fulfill all of the following criteria:

1. Provision of informed consent.
2. Scheduled for primary or secondary, cemented or non-cemented, total hip arthroplasty.
3. Classified as ASA Physical Status Classification System class P1, P2 or P3 according to the American Society of Anaesthesiology.

#### 3.3.3 Exclusion criteria

Any of the following is regarded as a criterion for exclusion from the study:

1. Involvement in the planning and conduct of the study (applies to both Astra Tech staff or staff at the study site).
2. Previous enrolment or randomisation of treatment in the present study.
3. Expected or confirmed participation in another clinical study, that may interfere with the present study, during the study period.
4. Suspected severe non-compliance to protocol as judged by the investigator.
5. Current symptoms of haemophilia.
6. Current symptoms of hyperkalaemia.
7. Current symptoms of systemic infection or local infection in the operation field.
8. Current symptoms of impaired renal function including creatinine/clearance levels above the normal reference values.
9. History of or presence of malignant disease with propensity for systemic spread during the last 5 years.
10. Current or expected use of cytotoxic drugs.

11. Current untreated anaemia (e.g. sickle cell anaemia), i.e. Hb concentration < 11 g/dl (7 mmol/l).
12. Use of recombinant erythropoietin.
13. Use of aprotinin and/or fibrin sealant.
14. Use of other autologous blood transfusion than that with the Sangvia® system (e.g. CellSaver, pre-donation, acute normovolemic haemodilution etc.).
15. Women of childbearing age.
16. Fractures
17. Revision/secondary total hip surgery with expected serious bone grafting

### 3.3.4 Restrictions

Use of tranexamic acid (cyclokapron) is allowed as long as it is used for all included patients at the individual clinic.

### 3.3.5 Discontinuation of subjects from treatment or assessment

#### 3.3.5.1 Criteria for discontinuation

Subjects may be discontinued from study treatment and study specific assessments at any time. Specific reasons for discontinuing a subject from this study are:

- Voluntary discontinuation by the subject who is at any time free to discontinue his/her participation in the study, without prejudice to further treatment
- Safety reasons as judged by the investigator and/or Astra Tech, e.g. new safety information.
- Severe non-compliance to protocol as judged by the investigator and/or Astra Tech
- Incorrect enrolment i.e., the subject does not meet the required inclusion/exclusion criteria for the study
- Subject lost to follow-up

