#### 3.3.5.2 Procedures for discontinuation

Subjects who discontinue should always be asked about the reason(s) for their discontinuation and the presence of any adverse events. If possible, they should be seen and assessed by an investigator. Adverse events shall be followed up.

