#### 4.2.1.2 Derivation or calculation of variable

Need for allogeneic blood transfusion will be expressed as transfusion rate in percentage, i.e. number of subjects with allogeneic blood transfusion/total number of subjects, and as the total volume amounts (in ml and expressed as units) of allogeneic blood transfused per treatment group. A transfusion index (units per transfused patient) will also be calculated.

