#### 6.1.3 Handling of dropouts and missing data

Subjects dropping out from the trial before surgery will be replaced. Subjects dropping out after surgery during the recruitment period will be compensated for using continuous recruitment. Subjects dropping out after surgery and after the completion of the recruitment period will be compensated for in the sample size estimation, see section 6.5.

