## 6.2 Description of outcome variables in relation to objectives and hypotheses

The primary variable, transfusion rate, will be measured as the proportion ( $\pi$ ) of patients in each treatment group that is receiving allogeneic blood transfusion of the total number of patients in each treatment group. The hypothesis to be tested is:

$$H_0 = \pi_s = \pi_c$$

versus

$$H_1 = \pi_s \neq \pi_c$$

Where:

$\pi_s$  = Proportion patients treated with Sangvia® that require allogeneic blood transfusion in addition to Sangvia® transfusion.

$\pi_c$  = Proportion patients in the control group that require allogeneic blood transfusion.

The hypothesis will be tested using the Fischer Exact Test. The hypothesis will be rejected if the p-value is  $\leq 0.05$ .

Secondary objectives will be tested using similar hypotheses. The total and variable specific proportion values for infection rate, use of post-operative antibiotics and adverse events will be tested between the groups using the Fischer Exact Test. Continuous variables (e.g. post-op Hb values) will be compared and tested using the Wilcoxon Rank Sum test. Laboratory blood markers will also be evaluated for changes over time within each treatment group and this change will be tested using the Wilcoxon Signed Rank test.

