## 6.5 Determination of sample size

The primary variable and objective is the base for the sample size calculation. The sample size formula used is referred to in Lachin 1981.

$$N = \frac{(Z_{\alpha} + Z_{\beta})^2 4\bar{\pi}(1 - \bar{\pi})}{(\pi_s - \pi_c)^2}$$

Where:

N = total number of patients

$Z_{\alpha} = 1.96$  ( $\alpha = 0.05$ )

$Z_{\beta} = 1.2816$  ( $1 - \beta = 0.90$ )

$$\bar{\pi} = \frac{\pi_s + \pi_c}{2}$$

An estimation normal use of allogeneic blood of 21% is based on reported values in the literature. It is acknowledged that in revision surgery a higher percentage of allogeneic blood transfusions is seen than in primary total hip replacements. Because revision patients requiring serious bone grafting are excluded, the percentage of revision patients is expected to be just slightly higher than for the average primary total hip. A high number of revision, e.g. a maximum of 30%, in the total group of patients is considered to have limited effect of the total transfusion rate but are accounted for in the 21% assumed for the total group. The expected values of transfusion rate in the Sangvia® group is estimated to lie around 7%. Accordingly, imputing the values for the estimated transfusion rates in the test and control group generates a mean transfusion rate value of 14%. The sample size necessary for detection of this expected difference in transfusion rate frequency is calculated to 260 patients (5% significance level, two-sided hypothesis, 90% power). Additional 40 patients will be included in the study to compensate for drop-out. In summary, 300 patients will be included in total and 150 in each treatment group.

The transfusion rate of bank blood is considered to vary dependent on type and complexity of surgery. Greatest normal use and differences between the groups are expected in the subgroup with medium (surgery duration 1-2 hours) to complex (surgery duration more than 2 hours) surgery complexity why power are considered to be adequate for the planned subgroup analyses in these groups.

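### The primary hypothesis defines the test-arm transfusion rate only for patients who received Sangvia blood, but the control rate over the whole control group

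*Protocol*

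**What the plan says.** **Primary hypothesis.** The opening sentence of section 6.2 takes the transfusion rate over the total number of patients in each treatment group. Section 4.2.1.2 agrees: "number of subjects with allogeneic blood transfusion/total number of subjects". The symbols in H0 and H1 are then spelled out. The test-arm parameter is "Proportion patients treated with Sangvia® that require allogeneic blood transfusion in addition to Sangvia® transfusion". The control parameter is the proportion of the control group that needs allogeneic blood, with no condition on treatment received.

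**Reinfusion not given or not completed.** Section 3.1 lets the investigator make an exception to routine return of the collected blood where the individual patient's risk is judged to be increased. Section 3.2.1 adds: "Any signs of a serious clinical event will abort the transfusion". Section 3.4.2, by contrast, has collected blood returned to the patient without exception.

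**Discontinuation.** Section 3.3.5.1: "Subjects may be discontinued from study treatment and study specific assessments at any time". The listed grounds include safety, severe non-compliance and incorrect enrolment, as well as the patient's own wish. Section 3.3.5.2: "Subjects who discontinue should always be asked about the reason(s) for their discontinuation and the presence of any adverse events". It also asks for a visit to an investigator if possible and for follow-up of adverse events. It does not mention the allogeneic transfusion log.

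**Drop-outs and analysis sets.** Section 6.1.3: "Subjects dropping out after surgery during the recruitment period will be compensated for using continuous recruitment". Section 6.3 puts all patients in the APT set but bases efficacy conclusions on the per-protocol set.

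**The concern.** The two parameters compared by the primary test do not describe the same kind of population. Read literally, a test patient who got bank blood but no salvaged blood either falls outside the test-arm proportion altogether or sits in it as a non-event. No control patient can be affected, because controls have no reinfusion to withhold or abort.

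Patients whose reinfusion is withheld or aborted have been judged at increased risk or have shown signs of a serious event. They may well need bank blood more often than average. Leaving out their transfusions would lower the reported test-arm rate and leave the control rate untouched. This bears on the primary hypothesis itself.

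The discontinuation text raises a related point about data. If the transfusion log were not continued for a patient taken off study treatment, the outcome could not be recovered later by choosing a different analysis set.

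**Working it through.** **1. The plan's own figure.** Section 6.5 assumes 21% ("An estimation normal use of allogeneic blood of 21% is based on reported values in the literature") against 7%, with "5% significance level, two-sided hypothesis, 90% power". The mean rate is 14%, so N = (1.96 + 1.2816)² × 4 × 0.14 × 0.86 / 0.14² = 258.2, in line with the stated 260. Adding 40 for drop-out gives 300, or 150 per arm. There is no arithmetic error.

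**2. The definitions side by side.**

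| Place | Test arm | Control arm |
|---|---|---|
| 6.2, opening sentence | all patients in group | all patients in group |
| 4.2.1.2 | all subjects | all subjects |
| 6.2, parameters of H0 and H1 | those treated with Sangvia who need bank blood on top of it | all patients in group |

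The third row contradicts the first two, and in one arm only.

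**3. Analysis set.** Section 3.1 makes a withheld reinfusion a permitted exception, while section 3.4.2 leaves no room for one. The protocol therefore does not settle whether such a patient has a major deviation and leaves the per-protocol set, on which efficacy conclusions rest.

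**4. Inputs for size.** From the protocol: 150 per arm, 21% control rate, two-sided Fisher test at p ≤ 0.05. Assumed, because the protocol gives neither: a share d = 5% to 10% of test patients affected, and a transfusion risk q = 21% to 50% among them.

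**5. Effect on the test-arm rate if the other test patients run at the planned 7%.**
- Transfusions not counted = 150 × d × q, from 150 × 0.05 × 0.21 = 1.6 to 150 × 0.10 × 0.50 = 7.5.
- Rate over everyone = (1 − d) × 7% + d × q, from 7.7% to 11.3%.
- Reported rate if affected patients stay in the denominator as non-events = (1 − d) × 7%, that is 6.7% down to 6.3%. If they are removed from both counts, it is 7.0%.

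**6. Chance of a false result favouring the device when both arms are truly at 21%.** This is the sum, over all pairs of counts (x test, y control), of Bin(x; n, p) × Bin(y; 150, 0.21), taken where the Fisher p-value is ≤ 0.05 and the test rate is the lower. With full counting (n = 150, p = 21%) it is 1.8%. The three readings are:
- Non-events: p = 0.21 − d × q, n = 150.
- Removed: p = (0.21 − d × q) / (1 − d), n = 142 or 135.
- Replaced by patients like those who remain: the same p as removed, n = 150.

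| d | q | Non-events: p | Chance | Removed: p | Chance | Replaced: chance |
|---|---|---|---|---|---|---|
| 5% | 21% | 20.0% | 3.0% | 21.0% | 2.2% | 1.8% |
| 5% | 50% | 18.5% | 5.9% | 19.5% | 4.5% | 3.8% |
| 10% | 21% | 18.9% | 5.0% | 21.0% | 2.1% | 1.8% |
| 10% | 50% | 16.0% | 15.9% | 17.8% | 8.7% | 8.0% |

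At q = 21%, removing or replacing patients causes no bias. The 2.1% and 2.2% only reflect the discreteness of the Fisher test at a smaller test arm.

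**The case against.** The strongest reply is that the operative definition appears twice, symmetrically, and that the parameter text in 6.2 is loose shorthand for the test arm's planned treatment. That may well be what was meant. But the shorthand is attached to the symbols in H0 and H1, so it needs correcting rather than interpreting.

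A reader might also infer three stronger things that the documents do not support.

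- **That stopping reinfusion ends study assessments.** Section 3.3.5.1 is permissive, its parent heading speaks of treatment or assessment, its grounds are for leaving the study, and it applies to both arms. Sections 3.1 and 3.2.1 do not describe a withheld or aborted reinfusion as discontinuation. Section 3.2.1 goes on to say that subjects are closely followed in hospital and checked at 2 months. Section 4.2.1.1 registers every allogeneic transfusion during the study period. What stands is narrower: the procedure for discontinued subjects does not say that the log continues.
- **That replacement deletes drop-outs.** Sections 3.5 and 6.1.3 add patients, and section 6.3 keeps everyone in the APT set. Nothing removes the outcome of a patient who leaves after surgery. What stands is that their place in the efficacy analysis is not stated.
- **That the error is about 16%.** That is the worst corner of one reading. Taken literally, restricting the parameter to patients treated with Sangvia also restricts the denominator, which points to the removed column and its lower figures.

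**Conclusion.** The inconsistency is real and should be corrected. Section 6.2 conditions the test-arm parameter on treatment received, does not do so for control, and contradicts both its own opening sentence and section 4.2.1.2. The patients it would affect are ones the protocol foresees. Any loss through this wording is one-sided.

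The size cannot be fixed from the protocol, since it rests on an assumed affected share of 5% to 10% and an assumed risk of 21% to 50%. On those assumptions, with 21% in both arms and 150 per arm, the 1.8% chance of a false result favouring the device becomes 3.0–15.9% (non-events), about 2.1–8.7% (removed) or 1.8–8.0% (replaced). The low ends show little or no harm; the high ends would matter.

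The silence on the transfusion log in section 3.3.5.2 is a secondary point. It leaves a gap in the instructions, but it does not show that outcome data would go uncollected.

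**What to change.** 1. In section 6.2, define the test-arm parameter as the proportion of all patients randomised to Sangvia who receive any allogeneic blood, whether or not salvaged blood was returned. This matches section 4.2.1.2 and mirrors the control parameter.
2. In section 3.3.5.2, state that unless consent for data is withdrawn, allogeneic transfusions are recorded to discharge in both arms after study treatment stops, whatever the reason.
3. In sections 3.5 and 6.1.3, state that patients who leave after surgery stay in the analysis of their assigned group even when additional patients are recruited.
4. Reconcile section 3.1 (exceptions to returning collected blood) with section 3.4.2 (no exception), so that it is clear whether a withheld reinfusion is a protocol deviation for section 6.3. Which clinical rule applies is for the sponsor.

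The cost is protocol wording and slightly more data collection, mostly for patients who may still be in hospital. The test-arm rate may come out slightly higher, which is the price of counting every randomised patient.

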#### 3.3.5.2 Procedures for discontinuation

Subjects who discontinue should always be asked about the reason(s) for their discontinuation and the presence of any adverse events. If possible, they should be seen and assessed by an investigator. Adverse events shall be followed up.

#### 3.3.5.3 Procedures for handling incorrect enrolled subjects

Subjects not meeting the inclusion/exclusion criteria for a study should, under no circumstances, be enrolled into the study - there can be no exceptions to this rule. Incorrect enrolled subjects will

not be included in the per protocol analysis set or in the efficacy conclusions and no financial compensation will be given for these subjects.

## 3.4 Treatments

### 3.4.1 Identity of investigational product and comparators

The investigational product is the CE-marked Sangvia® Blood Salvage System. The system consists of an intra-operative set, a post-operative set and vacuum tubing that enable collection, filtration and transfusion of intra-operative and post-operative blood.

[figure not shown]

The recommended user instructions for the Sangvia® Blood Salvage System should be followed for set-up, blood collection and reinfusion.

In summary, the collection canister is connected to a suction source with the recommended suction pressure of 100 mmHg (maximum 150 mmHg is allowed) and a suction tip is connected to the inlet tubing of the system. The collection unit is placed lower or at the same height as the operation table and an anticoagulant drip is connected to the system (ACD-A, sodium citrate or CPD) with the recommended ratio of 1:7 (approximately 20 drips per minute). The blood is filtered from larger debris, cement and bone particles by a macro filter of 200µm when collected in the chamber. The upper compartment of the collection unit has a maximum volume of 700 ml and the lower compartment has a maximum volume of 500 ml. When blood is being emptied to the transfusion bag the opening between the upper and the lower compartments should be closed. The blood is filtered from small particles by a micro filter before reinfusion. The reinfusion is initiated when 500 ml blood have been collected or at the end of surgery. Blood transfusion should be completed within 6 hours of the start of collection. Post-operative collection and transfusion will follow after surgery. The post-operative set is set-up and used according to the recommended user instructions. As for the intra-operative collection phase blood transfusion must be completed within 6 hours from start of collection during the post-operative phase. The reinfusion of the post-operatively collected blood may start either when the blood has passed 500 ml in the lower chamber or at the end of the 6 hour collection period. Not more than 2500 ml intra- and/or postoperatively collected blood in total should be transfused to the patients.

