## 1.1 Background

Allogeneic blood transfusions subject patients to risk of infection, allergic reactions, immunosuppression and are also associated with high costs. A variety of alternatives to allogeneic blood transfusions have been proposed, such as the use of solutions to support oxygen transport, human recombinant erythropoietin, intra-operative autologous blood collection, normovolemic hemodilution, preoperative blood salvage and postoperative infusion of shed wound blood. At present autotransfusion is the most commonly used alternative to allogeneic blood transfusions and the application of the autotransfusion techniques has increased along with a reduced need of allogeneic transfusion, reduced costs and minimized exposure to infectious agents. Although autologous blood is proven to be a safe transfusion product it represents only a small percentage of the total amount of blood transfused.

A number of autotransfusion devices are commercially available. The techniques of peri-operative autotransfusion can be subdivided depending on the extent to which the scavenged blood is processed prior to transfusion. In “filtered autotransfusion systems”, the blood is often anticoagulated and filtered, whereas “washed autotransfusion systems” use anticoagulation, cell separation, washing and filtration. Filtered autotransfusion systems collect and transfuse whole blood. Blood is collected from the surgical wound through a suction device or drain and actively aspirated to a reservoir. This reservoir has a macro filter (e.g. 20-150 µm) to remove large particles and cellular debris from the blood. A regulated negative pressure of no more than 150 mmHg is recommended to provide the suction necessary during blood collection. Larger negative pressures are believed to increase haemolysis. If applicable, the aspirated blood is anticoagulated either at the point of collection or in the reservoir. Even without anticoagulation, the blood collected for postoperative autotransfusion does not usually clot as it is defibrinogenated. The blood should be transfused within 6 hours of collection to preserve cellular viability and reduce the risk of infection.

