### **Post-operative follow-up**

#### 3 ( $\pm$ 1) hours after end of surgery

- Surgery stop time will be registered in the CRF
- The estimated intra-operative and post-operative blood loss volumes will be registered in the blood loss log.
- Any allogeneic and/or autologous blood transfusions will be registered in the allogeneic and/or the autologous transfusion logs.
- The Sangvia® postoperative drain (test group) and the Bellovac drain (control group) connection time will be registered.
- Venous blood sample/s will be taken from each subject before return of post-operative autologous blood if applicable for analyses of Hb, Hct/EVF,  $\text{Na}^+$ ,  $\text{K}^+$ , TPC, CRP, LPC, creatinine and Glomerular Filtration Rate (GFR)/Creatinine Clearance ( $\text{C}_{\text{Cr}}$ ).
- For the patients randomized to the Sangvia® treatment group postoperative blood salvage will be stopped, returned and the kit disconnected within 6 hours after activation. The drain will remain connected until the first post-operative day. In total, the transfusion volume of 2500 ml must not be exceeded when combining the intra- and postoperatively collected autologous blood.
- Drainage will continue in both treatment groups.
- Any allogeneic and/or autologous blood transfusions will be registered in the allogeneic and/or the autologous transfusion logs.
- Presence of SIRS will be evaluated.

- Vital signs (blood pressure, body temperature and heart rate) will be registered.
- Any additional adverse events and/or medications will be registered in applicable logs.
- Clinical signs or symptoms of general and/or wound infection will be registered.

Day 1 - first post-operative morning, 24 ( $\pm 6$ ) hours after end of surgery

- Venous blood sample/s will be taken from each subject 24 hours after end of surgery for analyses of Hb, Hct/EVF,  $\text{Na}^+$ ,  $\text{K}^+$ , TPC, CRP, LPC, creatinine and Glomerular Filtration Rate (GFR)/Creatinine Clearance ( $\text{C}_{\text{Cr}}$ ).
- The estimated additional post-operative blood loss volume will be registered in the blood loss log, if applicable.
- Drainages in both treatment groups will be removed.
- Any additional allogeneic blood transfusions will be registered in the allogeneic transfusion log.
- Presence of SIRS will be evaluated
- Vital signs (blood pressure, body temperature and heart rate) will be registered.
- Any additional adverse events and/or medications will be registered in applicable logs.

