### 3.4.2 Treatment regimens

The subjects included in the study will be randomized to either receive blood transfusion with Sangvia® (test group) or to a group where only allogeneic blood transfusion is used if necessary (control group). In the test group the intra-, and if applicable also the post-operative blood, collected with Sangvia® will always be returned to the patient. In the control group allogeneic blood transfusion will be given if transfusion triggers have been fulfilled and/or if the clinical symptoms justify transfusion. Allogeneic blood transfusion is also allowed to be given in the test group in addition to the Sangvia® blood if transfusion triggers have been fulfilled and/or if the clinical symptoms justify transfusion. Every decision to give allogeneic blood transfusion must whenever possible be taken by an assessor, unaware of the treatment group, and based on his/her opinion of the complete clinical picture for the individual patient. In addition, the reason for a transfusion must always be registered in the CRF.

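### The fallback start time for post-operative reinfusion, at the end of the 6-hour collection period, cannot meet the protocol's own 6-hour completion limit

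*Protocol*

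**What the plan says.** Section 3.4.1 summarises how the device is used. For the post-operative phase it sets a deadline: "blood transfusion must be completed within 6 hours from start of collection during the post-operative phase". The sentence that follows says reinfusion "may start either when the blood has passed 500 ml in the lower chamber or at the end of the 6 hour collection period".

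Three other places bear on the same step:

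- Section 3.1, in the instructions for 3 (±1) hours after surgery, says post-operative salvage "will be stopped, returned and the kit disconnected within 6 hours after activation". It also places the 3-hour blood sample "before return of post-operative autologous blood if applicable".
- Section 3.4.2 says the collected blood "will always be returned to the patient". Section 3.1 allows an exception only where the investigator sees an increased risk for the individual patient.
- Section 1.1 gives the reason for a time limit: "The blood should be transfused within 6 hours of collection to preserve cellular viability and reduce the risk of infection".

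**The concern.** Two consecutive sentences in section 3.4.1 cannot both be followed when the post-operative collection stays at or below 500 ml. The volume criterion is then never met, so the only start point listed is hour 6, which is also the deadline for completion.

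A site that follows the listed fallback returns filtered, unwashed blood after the limit that the protocol sets. A site that follows section 3.1 has to stop collecting earlier, but section 3.4.1 lists no earlier start for small volumes. Routine return of the blood means that discarding a late collection is not the default way out. Patient safety and clear site instructions are at stake, not a statistical result.

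**Working it through.** **Inputs**

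- Deadline for completed return: 6 h from start of post-operative collection (section 3.4.1).
- Listed start points: more than 500 ml in the lower chamber, or hour 6 (section 3.4.1).
- Sample to be taken before post-operative return: 3 h ± 1 h after end of surgery, so 2 to 4 h (section 3.1).
- Reinfusion time *d*: not given in the protocol. Assumed values are 0.5, 1 and 2 h, for illustration only.

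**Step 1: collections that pass 500 ml.** Reinfusion can start before hour 6, so the deadline can be met. There is no conflict in this branch, provided the start is early enough.

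**Step 2: collections that do not pass 500 ml.** With time 0 at the start of collection, completion = start + *d* = 6 + *d*. This exceeds 6 for every *d* > 0, so the conflict does not depend on the assumed values. To comply, the start must be no later than 6 − *d*.

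| Assumed *d* (h) | Return ends if started at hour 6 (h) | Overrun (h) | Latest compliant start (h) |
|---|---|---|---|
| 0.5 | 6.5 | 0.5 | 5.5 |
| 1 | 7 | 1 | 5 |
| 2 | 8 | 2 | 4 |

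**Step 3: comparison with section 3.1.** That section puts stopping, return and disconnection all inside 6 h of activation. It agrees with the completion rule in section 3.4.1 and rules out a start at hour 6.

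**Step 4: does an earlier start leave room for the 3-hour sample?** Post-operative collection follows surgery, so the tightest case is activation at end of surgery (assumption). A sample at 4 h leaves 6 − 4 = 2 h for return, and a sample at 2 h leaves 6 − 2 = 4 h. A reinfusion of up to 2 h therefore fits in every case, although with no slack when *d* is 2 h and the sample is taken at 4 h.

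**The case against.** The best counter-argument is that the protocol already shows which rule governs. The deadline is mandatory, the start clause is only permissive, and section 3.1 independently reaches the same result as the deadline. On this reading, one loosely worded clause sits beneath two binding statements that agree. Section 3.4.1 also presents itself as a summary of the device's user instructions, which are not shown and may tell sites what to do with small volumes.

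Much of this stands. It confines the error to one clause, and it means that no actual overrun at any site can be asserted. It does not repair the clause: the permissive wording introduces a two-item list with no earlier start for small volumes, and no outside instruction can make the two sentences agree.

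Two narrower points also have force. Section 1.1 counts 6 hours from collection, not from the start of collection. With a start at hour 6 and a short reinfusion, only the earliest-drained blood would exceed that looser limit. The breach is therefore of section 3.4.1's own stricter clock, and the link to viability and infection applies most directly to that earliest fraction. The 2-hour reinfusion time is also an unsupported upper value for a volume that does not pass 500 ml, so the 8-hour figure should be read as the edge of an assumed range.

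**Conclusion.** The concern holds. For post-operative collections that do not pass 500 ml, the only start point listed in section 3.4.1 breaks the completion rule stated one sentence earlier and conflicts with section 3.1. This follows for any reinfusion time above zero.

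The overrun equals the reinfusion time: 0.5 to 2 h under the assumed range, with return ending at 6.5 to 8 h. How many patients this would affect cannot be worked out, because post-operative salvage happens only if bleeding continues and the protocol gives no distribution of volumes.

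It should be corrected as a safety wording error. It changes nothing in the primary outcome, the sample size or the planned analyses.

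**What to change.** In section 3.4.1, replace the second start option with a rule for collections that have not passed 500 ml: collection stops, and reinfusion starts, early enough for return to be complete within 6 hours of the start of collection. Use the same clock in sections 3.1 and 3.4.1, stating whether activation and start of collection are the same moment. Keep the 3-hour sample ahead of the return of post-operative blood.

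The exact latest start is for the sponsor's medical and device experts to set, consistent with the user instructions.

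The cost is one clause and a site instruction. No new data collection and no change to the analysis are needed.
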